### Study population

Patients are recruited from the outpatient diabetes clinic of the Erasmus Medical Centre in Rotterdam by the medical team, based on the in- and exclusion criteria shown in Table 1. In our hospital, a tertiary referral centre, we see both patients with only oral antidiabetic agents and patients treated with one or more insulin doses daily. In general, our patients will have more complex disease and more comorbidity compared to the average diabetic patient referred to a GP. How ever, GP’s can also directly refer their eligible patients to our trial. Patients interested in participating in the study will receive an information letter and a questionnaire to be filled in at home. Two weeks later they will visit the outpatient clinic for an intake interview with the researcher ([name]). Eligibility will be checked again. After signing the informed consent form by the patient, the baseline measurements will be performed.

**Table 1 T1:** Eligibility

Inclusion criteria:	
**1**	Diagnosed diabetes mellitus type 2
**2**	Age 18–75 years
**3**	BMI ≥ 27 kg/m^2^
Exclusion criteria:	
**6**	Pregnancy or lactation during the study
**7**	Inadequate expression of the Dutch language (spoken and written)
**8**	Inability to lose ≥ 5% of bodyweight during the first 8 weeks of VLCD
**9**	Severe psychiatric problems
**10**	Significant cardiac arrhythmias, unstable angina, decompensated congestive heart failure, major organ system failure, untreated hypothyroidism and/or myocardial infarction, end-stage renal disease, cerebrovascular accident or major surgery in the last 3 months.

Patients with psychiatric disorders or major psychological disturbances are excluded from the trial. Patients with eating disorders (bulimia nervosa and binge eating disorder) or depression are not excluded, since it is expected that these conditions are common among patients with type 2 diabetes and previous research has shown that cognitive behaviour therapy can have beneficial effects in these patient groups [28,41-43]. We will analyze the effect of these background variables on the outcome of the intervention.

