### Sample size calculation

After randomization of 75 participants, the sample size calculation was carried out by an independent statistician to base it on realistic data.

Sample size was calculated with SPSS 17.0, using the mixed-model ANOVA procedure described by Aberson [44].

Alpha was set at 0.05, power at 0.80 and the baseline-end correlation at 0.90. A clinically relevant difference between the treatment groups is 5% weight loss [3]. Mean weight at the start of the treatment is about 110 kg, with a standard deviation of 22, this equals an effect size of d = 0.25.[45] With this power calculation we estimate that we need 52 patients in each group. Anticipating a dropout rate of 25%, we aim for a total sample size of 140.

For the most important secondary outcomes we calculated the detectable difference with the sample size of n=104, alpha 0.05 and power 0.80 (Table 2). The detectable differences are quite small, so the aimed sample size seems adequate to analyse at least these secondary outcomes.

**Table 2 T2:** Power calculation secondary outcomes

**Secondary outcome:**	**SD:**	**Detectable difference:(n = 104, β=0.8 α=0.05)**
Waist circumference	11	2.75 cm
Blood pressure sys/dias	20/20	5/5 mmHg
Total cholesterol	1.4	0.35 mmol/l
LDL cholesterol	1.0	0.25 mmol/l
HDL cholesterol	0.7	0.2 mmol/l
Triglyceride	3.0	0.75 mmol/l
HbA1c	12	3 mmol/mol
Insulin	50	12.5 IU
Depression (HADS score 0–21)	3	0.75
Anxiety (HADS score 0–21)	4	1.0
Self esteem (RSE score 10–40)	5	1.25
Fatigue (CIS score 8–56)	13	3.25
Concentration (CIS score 5–35)	8.5	2.1
Motivation (CIS score 4–28)	6	1.5
Activity (CIS score 3–21)	5	1.25
Quality of life (EuroQol 5D score 1–3)	0.5	0.125
Quality of life (EuroQol VAS 1–100)	21	5.25

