We have developed a protocol for the use of a VLCD in patients with type 2 diabetes, where we describe the different aspects of the treatment. Oral anti-diabetic agents (except Metformin) and short-acting insulin analogues are discontinued, while the dosage of long-acting insulin analogues and biphasic mixtures is halved, to avoid severe hypoglycaemia. GLP-1 or DPP-4 inhibitors will be continued. During the VLCD and gradual transition to a normal diet, medication is adjusted by means of glucose self-control and frequent contact with diabetes nurses and dieticians. The dose of any antihypertensive medication is also adjusted during VLCD and follow-up, in consultation with the responsible physician.

Realimentation takes place by slowly reintroducing normal food in 12 weeks time, until participants use a lightly energy restricted diet (1300 kcal a day), according to national dietary guidelines. 

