#### Secondary outcomes

1. Anthropometric measurements: Height is measured to the nearest 0.5 cm without shoes using a Seca stadiometer. Body Mass Index is calculated as weight divided by height squared (BMI = weight (kg)/height (m)^2^). Waist circumference (cm) is measured at the level midway between the lowest rib margin and the aliac crest. Hip circumference is measured at the widest point over the buttocks. Both waist- and hip circumference are measured by the nearest 0,5 cm, using a tape-measure. Subsequently, waist-hip ratio (WHR) is calculated.

2. Cardiovascular riskprofile by use of the UKPDS risk engine [49]:

a. Systolic and diastolic blood pressure (mmHg) are measured twice in upright position, while the patient had rested for at least 5 minutes with an Omron M4-I Intelli-sense device. The second value will be used.

b. Blood samples are taken to asses total cholesterol, LDL-cholesterol, HDL-cholesterol and triglycerides (mmol/l), measured on a Roche Modular P 800, reagents used from Roche, methods used from Roche are Cholesterol Chod-pap, HDL-c plus 3^rd^ generation, LDL-c plus 2^nd^ generation and Triglycerides GPO-PAP.

3. Glycaemic control:

a. HbA_1c_ (mmol/mol), measured on a Menarini HA-8160, reversed-phase action exchange chromatography.

b. HOMA-%S calculated by measuring fasting plasma glucose (mmol/l), (measured on a Roche Modular P 800, reagent used from Roche, method used from Roche is Glucose Hexokinase) and fasting insulin (mmol/l)

c. Glucose lowering medication (insulin (IU/day) and antidiabetic agents (mg/day))

4. Psychological measurements

a. Anxiety and depression are measured by the Hospital Anxiety and Depression Scale (HADS)[50,51]. The HADS consists of a 7-item Anxiety scale and a 7-item Depression Scale. The items are scored from 0 to 3 and the range of scores is 0 – 21. A score between 0 and 7 excludes depression/anxiety. A score of 8–10 indicates a possible depression/anxiety. A score of 11–21 is indicative of a probable depression/anxiety.

b. Somatic symptoms are measured by the VOEG-13 (‘Vragenlijst Onderzoek Ervaren Gezondheid’) [52], a Dutch 13-item questionnaire used to measure the health of a population, often used in social science research. The items consist of somatic symptoms like headache, nervousness and lethargy and respondents indicate whether they have these symptoms or not. A higher score indicates more somatic symptoms and a worse perceived health.

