	**Baseline (n=13)**	
**Sex (%)**	Males	25%
	Females	75%
**Age (y)**		49.5
**Insulin dependant (%)**	Insulin dependant	75%
	Non-insulin dependant (OAD)	25%

**Table 5 T5:** Outcome measurements pilot group

	**Baseline (n=13)**	**T1 = 4 months (n=13)**	**95%CI**
**Weight (kg)**	114.8	106.0***	[5.2-12.4]
**Waist circumference (cm)**	121.4	113.7**	[3.2-12.2]
**Systolic BP (mmHg)**	144.6	127.9*	[1.1-32.2]
**Diastolic BP (mmHg)**	86.1	78.0	[−0.4-16.7]
**Total cholesterol (mmol/l)**	5.0	4.5	[−0.2-1.3]
**HDL cholesterol (mmol/l)**	1.7	1.3	[−0.3-1.3]
**LDL cholesterol (mmol/l)**	2.6	2.5	[−0.3-0.5]
**Triglycerides (mmol/l)**	3.6	2.6	[−1.1-3.0]
**HbA1c (mmol/mol)**	66.3	66.6	[−9.8-9.1]
**Insulin (IU)**	82.3	32.3*	[7.3-94.7]
**Depression score (HAD)**	5.7	4.6	[−1.5-3.7]

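### HOMA-%S is defined from measured fasting insulin with no provision for insulin-treated participants, in whom it is confounded by injected insulin; the printed insulin unit is also wrong

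*Protocol article*

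**What the plan says.** Under Secondary outcomes, Glycaemic control, item 3b reads "HOMA-%S calculated by measuring fasting plasma glucose (mmol/l") "and fasting insulin (mmol/l"). The analyser, reagent and method are given for glucose. For insulin no assay is named. C-peptide is not mentioned, and nothing is said about participants who inject insulin. Item 3c, in the same domain, makes daily insulin dose an outcome in its own right.

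Insulin-treated patients belong to the trial population. Under Study population the clinic is described thus: "we see both patients with only oral antidiabetic agents and patients treated with one or more insulin doses daily". Table 1 has no exclusion for insulin use. In the pilot, Table 4 gives 75% insulin dependent, and Table 5 gives a mean dose with "Insulin (IU) 82.3 32.3* [7.3-94.7"] from baseline to 4 months. Table 2 carries insulin dose as a powered secondary outcome: "Insulin 50 12.5 IU".

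The dose changes during the trial. Under Phase 0, "short-acting insulin analogues are discontinued, while the dosage of long-acting insulin analogues and biphasic mixtures is halved"; medication is then adjusted individually through the VLCD and the return to a normal diet. According to Outcome assessment, baseline is taken before the VLCD and the next full assessment is at 4 months. According to Design of the study, only weight is measured at the 8-week randomisation visit.

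**The concern.** HOMA-%S infers insulin sensitivity from the fasting balance between glucose and the patient's own insulin. In someone who injects insulin, the measured concentration can include injected insulin, so the index partly reflects the prescribed dose. At a given glucose, a lower dose lowers measured insulin and raises HOMA-%S even if sensitivity has not moved.

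Two comparisons are exposed. Every change from baseline spans the VLCD dose cut, because there is no HOMA-%S value at randomisation. The between-arm contrast is exposed if insulin doses diverge after randomisation. The Discussion expects medication to fall if the intervention works, and item 3c measures this. An effect of CPI on dose could then appear a second time as an apparent effect on sensitivity, and the two would look like separate evidence.

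The printed unit is a separate error on the same line. Fasting insulin is given in mmol/l, the unit used for glucose, which is not plausible for an insulin concentration. A wrong unit in the input would make the calculated index wrong for every participant.

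**Working it through.** **Inputs from the protocol article.**
- Pilot mean insulin dose 82.3 IU at baseline and 32.3 IU at 4 months (Table 5).
- Insulin dose SD 50 and detectable difference 12.5 IU (Table 2).
- Pilot share on insulin 75%, n = 13 (Table 4).
- Evaluable sample 104 (Sample size calculation).

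**The plan's own figure.** The sample size section uses an effect size of 0.25. For insulin dose, 0.25 × 50 = 12.5 IU, so Table 2 is reproduced. This is a detectable difference, not an expected one; it is used below only to set a scale.

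**Assumptions, not in the documents.** HOMA-%S is proportional to 1/(glucose × insulin). Glucose and the patient's own insulin are held fixed. A share f of measured fasting insulin is injected insulin that the assay detects, and this part is proportional to dose. The documents do not give f, so it is varied. If the dose is multiplied by q, then

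HOMA-%S ratio = 1 / [(1 − f) + f × q].

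**Between arms, one arm 12.5 IU lower.** Dose 32.3 IU versus 32.3 − 12.5 = 19.8 IU, so q = 19.8/32.3 = 0.613.
- f = 0: ratio 1.00
- f = 0.25: 1/(0.75 + 0.153) = 1.11
- f = 0.50: 1/(0.50 + 0.307) = 1.24
- f = 0.75: 1/(0.25 + 0.460) = 1.41

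These ratios are for insulin users. An average over a whole arm that includes non-users would be closer to 1.

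**Change from baseline, if the dose falls as in the pilot.** The fall is 82.3 − 32.3 = 50.0 IU, or 50.0/82.3 = 61%, so q = 32.3/82.3 = 0.392.
- f = 0: ratio 1.00
- f = 0.10: 1.06
- f = 0.25: 1.18
- f = 0.50: 1.44
- f = 0.75: 1.84
- f = 1: 2.55

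This is a within-group change. It includes the dose cut that both arms share before randomisation, so it does not measure between-arm bias.

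**How firm is the 75%?** 75% of 13 is 9.75, not a whole number; the count may be 9 of 12, 9 of 13 or 10 of 13. The exact 95% intervals are 43% to 95%, 39% to 91% and 46% to 95%. The share not on insulin could therefore be anywhere from about 5% to 61%.

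**Sample left after restriction.** At 25% not on insulin, 0.25 × 104 = 26 evaluable participants. Over the range 5% to 61%, this is about 5 to 63.

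**The case against.** The article gives HOMA-%S one line and states no analysis set for it; handling of insulin users could sit in a full protocol or SAP that is not shown. This stands in part: it would be wrong to say that the article declares the index valid for everyone. But the line does fix the inputs, and with measured fasting insulin as an input the problem follows unless a restriction is added.

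A reader might infer that HOMA-%S will follow dose instead of sensitivity. The documents do not support that. The index remains interpretable in participants without insulin. In users, the distortion depends on the injected share of measured insulin and on what the unnamed assay detects, and it could be nil.

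A reader might also take the 61% pilot fall in dose, with HbA1c almost unchanged (66.3 to 66.6 mmol/mol), as proof of an artefact with no change in sensitivity. That does not follow. Pilot weight fell by 114.8 − 106.0 = 8.8 kg, and the Background says that weight loss lowers insulin resistance. Similar HbA1c on much less insulin is also what a real gain in sensitivity would look like; the pilot cannot separate the two.

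The main-trial share on insulin is unknown, and the Limitations section says that patients referred directly by GPs often have less severe disease. Finally, HOMA-%S is absent from the abstract's outcomes and from Table 2, and dose and HbA1c are outcomes beside it. These points limit the consequence but leave the confounding in place.

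**Conclusion.** The point holds as confounding of a secondary outcome. As defined, HOMA-%S mixes insulin sensitivity with injected dose in insulin-treated participants, whom the trial enrols and whose doses it changes. Change from baseline is affected by the VLCD dose cut. That cut precedes randomisation and applies to both arms, so it does not by itself bias the comparison of arms; only later differences in dose between arms do.

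The size cannot be determined from the documents. Under the assumptions shown, with f from 0.25 to 0.75, a 12.5 IU arm difference starting from 32.3 IU gives a ratio of about 1.11 to 1.41 among users, and 1.00 if no injected insulin is detected. The insulin unit is wrong whatever the value of f. This should be put right before analysis, but the primary conclusion on weight does not depend on it.

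**What to change.** 1. Define the HOMA-%S analysis in participants not using insulin at baseline. Baseline precedes randomisation, so this selection cannot be influenced by the arm.
2. In that subgroup, report insulin starts by arm and show results both with and without visits after a start. Setting those visits to missing should not be the only analysis: starting insulin happens after randomisation, may differ by arm and may be related to sensitivity, so the exclusion may be informative.
3. For participants using insulin at baseline, report insulin dose and HbA1c, and do not interpret HOMA-%S as insulin sensitivity.
4. Correct the fasting insulin unit, and name the assay, before the index is calculated.

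The work is small, since glucose-lowering medication is already recorded under item 3c. The real cost is precision: about a quarter of patients would remain if the trial resembles the pilot, roughly 26 of 104 and with wide uncertainty, so HOMA-%S would be descriptive. The primary outcome and the sample size are unchanged.

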## Methods/design

### Design of the study

This study is a randomized controlled parallel group intervention trial.

When patients lose equally or more than 5% of their bodyweight in the first 8 weeks of the VLCD, they are included in the intervention trial testing CPI. This arbitrary cut-off value was chosen because of its relatively large effect on the risk profile [3]. Moreover, we need a relevant weight loss to investigate weight maintenance after weight reduction. After randomization, stratified to the achieved weight loss at 8 weeks, participants are assigned to one of the following conditions:

1. VLCD + conventional treatment

2. VLCD + conventional treatment + CPI

The duration of the diet period will be 20 weeks: 8 weeks of VLCD (<800 kcal/day) followed by 12 weeks of slowly reintroducing a normal, mildly energy-restricted diet (1300 kcal/day). During week 10 of the diet, the intervention group starts with a total of 17 sessions of CPI. The first 10 sessions are weekly sessions; followed by two 2-weekly sessions, two monthly sessions, two 3-monthly sessions and 1 session with an interval of 6 months.

Outcome measurements are assessed at baseline, after finishing the intensive CPI-period at 4 months and subsequently at 1 year, 1,5 years and 2 years after randomization. At 8 weeks (randomization after VLCD), only the primary outcome (weight) will be measured.

Figure 1 shows the design of the study.

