### Outcome assessment

Outcome measurements (see below) are assessed at baseline (before start VLCD), and again at 4 months (after VLCD and 10 CPI sessions), 1 year, 1 ½ years and 2 years.

Demographic variables are assessed at baseline by use of a self-administered questionnaire, which is checked during the intake interview with the investigator.

All other secondary outcomes are assessed at baseline, after 4 months, 1 year, 1 ½ years and 2 years, using self-administered questionnaires, except of the Session Rating Scale, which is filled in after every CPI session.

Data are managed by use of the trial management system ‘EXPeRT Clinical’ of OmniComm, USA.

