b. Physical activity is measured using the SQUASH (Short Questionnaire to Assess Health Enhancing Physical Activity) [58]. The SQUASH collects days per week, average time per day, and effort for physical activities such as commuting activities, leisure time and sport activities, household activities, and activities at work or school. Total minutes of activity are calculated for each question by multiplying frequency (days per week) by duration (minutes per day). Activity scores for separate questions are calculated by multiplying total minutes of activity by an intensity score (range 1–9). The total activity score is calculated by taking the sum of the activity scores for the separate questions.

6. Cost-effectiveness

a. Quality of life is measured by the EuroQol (EQ-5D) [59,60]. The EQ-5D is 5-item self report questionnaire on which participants report if they experience any problems in mobility, self-care, usual activities, pain and anxiety/depression. Each dimension has 3 levels: no problems, some problems and severe problems. The scores on the three dimensions can be combined into one co called ‘utility’ score, which represents the societal value of quality of life. The utility score has a range from 1.00 (the value of health without health problems) till 0.00 (the value of health problems as bad a death). This societal value of quality of life is used as input for so called Quality Adjusted Life Years (QALY) analysis, as the societal perspective is the preferred perspective in health economics. The EuroQol instrument contains also the EQ-VAS, a vertical visual analogue scale with the anchors best imaginable health (score of 100) and worst imaginable health (score of 0). This EQ-VAS represents the patient’s perspective of quality of life.

b. Costs are measured by the Trimbos/iMTA Questionnaire for Costs associated with Psychiatric Illness (TiC-P) [61]. The TiC-P measures direct medical costs due to healthcare utilization during the past four weeks. Also, it registers the indirect non-medical costs due to productivity loss during the past two weeks.

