### Patient follow-up and compliance

Follow-up measurements will take place combined with evaluation group meetings.

For patients in both groups, follow-up visits to the physician, diabetes nurse and dietician are registered.

A common limitation of weight loss studies is a selective loss to follow-up: higher drop-out rates occur among patients, who do not achieve their weight loss goals. We want to tackle this problem by use of incentives to keep all patients in the trial: motivating phone calls of the researcher, little gifts during the program, etc.

Further more, we will perform a follow-up and analysis of the drop-outs after completion of the study and compare completers and drop-outs at base-line. For this purpose, the drop-outs will be interviewed by a medical student, who is not involved in the study.

Compliance to the intervention is assessed by registration of the attendance to the CPI sessions: participants are considered non-compliant when they are absent on more then 8 sessions. Since we expect that the treatment will be less effective when more then 8 sessions are missed, this non-compliant participants will be considered drop-outs.

We have conducted a pilot study to improve our research protocol. We will not perform interim analyses and we will not define stopping rules, since the intervention has no serious side-effects.

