## Discussion

To our knowledge, this trial is the first randomized controlled trial to test the effects of an integrated multi-model cognitive group therapy in the battle against weight regain after a successful weight loss intervention (VLCD) in patients with type 2 diabetes. Weight regain is common in the obese population in general, but even more pronounced in the diabetes type 2 population, and with more devastating effects on their health outcomes. The strength of this study is the combined psychological intervention (CPI) of cognitive restructuring, problem solving treatment and proactive coping, which will provide powerful tools to the participants for maintaining behavioral change and improving health outcomes. We expect that adding CPI to a VLCD will be effective in maintaining weight loss, improving lifestyle and, as a result, leading to improved glycaemic control and a reduction of cardiovascular risk.

We expect that a number of factors may influence the treatment effect, therefore we will also examine potential determinants of weight maintenance, such as depression, anxiety, self-esteem, fatigue, somatic symptoms, eating disorders and lifestyle. Apart from being predictive for the success of the intervention, these factors may be changed by the treatment itself and therefore will be followed over time as secondary outcome measurements.

It is expected that if the intervention is successful, it will also be cost effective since the costs of group counselling are relatively low and the expected reduction of medication, prevention or delay of complications and a reduction of hospital admissions are considered major cost savings. If the therapy is indeed effective, a formal cost effectiveness analysis will be performed.

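### Cost recall windows cover about 15% of follow-up time, and no other record of hospital admissions is described although fewer admissions are an expected major saving

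*Protocol article*

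**What the plan says.** All references are to the protocol article.

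- **Instrument.** Under Secondary outcomes, item 6 (Cost-effectiveness), costs are measured with the TiC-P: "The TiC-P measures direct medical costs due to healthcare utilization during the past four weeks". For work loss, "it registers the indirect non-medical costs due to productivity loss during the past two weeks".
- **Schedule.** Under Outcome assessment: "All other secondary outcomes are assessed at baseline, after 4 months, 1 year, 1 ½ years and 2 years, using self-administered questionnaires". Design of the study times the later visits "subsequently at 1 year, 1,5 years and 2 years after randomization". Four administrations therefore follow randomisation.
- **Where savings are expected.** The Discussion says that "the expected reduction of medication, prevention or delay of complications and a reduction of hospital admissions are considered major cost savings".
- **Other resource-use records.** Under Patient follow-up and compliance: "For patients in both groups, follow-up visits to the physician, diabetes nurse and dietician are registered". The same section registers attendance at the intervention sessions. The control-group section adds dietician visits and diet products over the 2 years, and visits to psychologists and other caregivers. Secondary outcomes, item 3, records daily insulin and antidiabetic doses.
- **Status.** Cost-effectiveness is the tertiary objective, and the Discussion makes the formal analysis conditional on the therapy being effective.

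**The concern.** The plan says where it expects money to be saved, then describes a collection method that sees one of those items, hospital admissions, for only about one week in seven. Admissions are rare and expensive. In a short window most patients have none. When the windows are scaled up to the full period, each admission inside one counts as 104/16 = 6.5 admissions, and each admission outside counts as zero. On average this can be right, but the result is noisy.

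This is more than analysis detail. How unobserved periods are costed can be settled later. An admission to another hospital that nobody asks about cannot be recovered by a later analysis plan. The conditional status does not help either: by the time effectiveness is known, follow-up is over.

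At stake is the precision of the cost comparison. The Limitations section uses the planned economic evaluation to support the usual-care comparator, and Future implementation makes cost-effectiveness a condition for promoting the programme.

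**Working it through.** The article states no coverage figure, so there is none to reproduce.

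**1. Share of follow-up time inside the windows**

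Inputs: recall of 4 weeks (medical) and 2 weeks (productivity); 4 visits after randomisation; 2 years = 104 weeks. The objective states no time horizon, so the 104 weeks are taken from the follow-up period.

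Coverage = visits × recall weeks / weeks of follow-up.

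- Medical use: 4 × 4 / 104 = 16/104 = 15.4%.
- Productivity: 4 × 2 / 104 = 8/104 = 7.7%.

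Sensitivity: counting follow-up from the baseline before the diet (112 weeks) gives 16/112 = 14.3% and 8/112 = 7.1%. Adding the baseline questionnaire and its own window gives 20/108 = 18.5% or 20/116 = 17.2% for medical use. The picture does not change.

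**2. Where the gaps fall**

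With visits at about weeks 17.4, 52, 78 and 104 after randomisation, the weeks outside the 4-week windows are:

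- before the first visit: 17.4 − 4 = 13.4
- then 52 − 17.4 − 4 = 30.6
- then 78 − 52 − 4 = 22
- then 104 − 78 − 4 = 22

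This takes the 4-month visit as counted from randomisation. The total covered does not depend on that.

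**3. Precision for admissions**

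The article gives no admission rate, so a range is assumed. It plans for 52 patients per group (Sample size calculation). Expected admissions per arm = 52 × 2 years × rate; expected number inside a window = that × 16/104. For equal arms under a Poisson model, SE(log rate ratio) = sqrt(4 / total events in both arms).

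| Assumed rate per patient-year | Per arm, 2 years | Per arm, in windows | SE, full capture | SE, windows |
|---|---|---|---|---|
| 0.1 | 10.4 | 1.6 | 0.44 | 1.12 |
| 0.2 | 20.8 | 3.2 | 0.31 | 0.79 |
| 0.3 | 31.2 | 4.8 | 0.25 | 0.65 |
| 0.5 | 52.0 | 8.0 | 0.20 | 0.50 |

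The ratio of the two standard errors is sqrt(104/16) = 2.55 at every rate.

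**4. Illustration**

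Assume 0.3 per patient-year in the control arm and a true 30% reduction.

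- Full capture: 31.2 against 21.8 admissions. SE = sqrt(1/31.2 + 1/21.8) = 0.28. The 95% interval around 0.70 is about 0.41 to 1.21.
- Windows: 4.8 against 3.4 admissions. SE = sqrt(1/4.8 + 1/3.4) = 0.71. The interval is about 0.17 to 2.8.

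With full capture, z = 0.36/0.28 ≈ 1.3, so even complete data would probably not show such a difference.

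**The case against.** **The windows are not the only record.** This stands. Clinic visits, caregiver visits, session attendance and glucose-lowering doses are all recorded separately. A reader might infer that about 85% of costs go unobserved. The documents do not support that: 85% is the share of weeks outside the medical windows, the share of costs cannot be derived from the article, and the separate records make it smaller. None of those records is described as covering admissions, however.

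**Spaced windows are a legitimate sample of time.** This also stands. Mean costs can be extrapolated or interpolated, so the loss is mainly one of precision. Bias would need the windows to be unrepresentative, which is possible with a gap of about 31 weeks but is not shown.

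**The 2.5-fold factor is not the factor for total costs.** Correct. It applies to Poisson counts of admissions seen only in windows. Items logged continuously are not inflated, and persistent differences between patients would lower the factor.

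**Full capture would still be imprecise.** Correct, as the illustration shows: the trial is sized for weight. That limits what the remedy can deliver. It does not justify giving up precision that is cheap to obtain.

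**This is a condensed article, and the full protocol may provide for chart extraction.** Possible. Its silence does not prove that admissions are lost. But the article states its cost instrument, windows and visit times explicitly, and describes no other source for an item that it calls a major saving.

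**Conclusion.** The point holds in a limited form. The recall windows cover about 15% of follow-up time for medical use and 8% for productivity loss, and no record of admissions outside them is described, although fewer admissions are an expected major saving. For admissions alone, the standard error of the between-arm comparison is about 2.5 times that with full capture. This assumes Poisson counts, four completed post-randomisation questionnaires per patient and a 104-week horizon. The event counts also rest on an assumed admission rate; the 2.5-fold ratio does not.

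A reader might conclude that the trial cannot answer its cost-effectiveness question. That goes too far: mean costs remain estimable, and several cost items are recorded outside the windows. The supported conclusion is that the admission component would be very imprecise. This is a cheap improvement for a tertiary, conditional objective. The primary result on weight is unaffected.

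**What to change.** - Keep the TiC-P for the other cost items.
- For every randomised patient, record hospital admissions (with days) and emergency visits from randomisation to 2 years from the hospital record.
- At each follow-up visit, ask about admissions elsewhere since the last visit. This matters most for patients referred by general practitioners.
- Use these full-period counts in the cost analysis in place of scaled-up four-week figures for the same items.
- State as a limitation that productivity loss still rests on two-week windows covering about 8% of follow-up.

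The cost is a little more data extraction, in a trial run from one hospital that already registers clinic visits in both groups, plus one extra question per visit. Admissions elsewhere would depend on recall over 4 to 8 months. Treatment, sample size and visit schedule do not change.
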